### Blinding (Masking)

Only the researcher in charge of administering the treatment (who opens the randomization envelopes) will be aware of the assigned intervention for each participant. The participants will be blinded because of the visual similarity of the treatments (LED on versus LED off). The researcher collecting the outcome data will also be blinded to the interventions and will not be present in the room during treatment. Group allocation will be disclosed only after the statistical analysis is completed, ensuring that the data collector and statistician remain blinded. Unblinding during the trial is not planned, as no adverse events are expected with PBM use.

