### Calibration/Training

A single examiner will assess five women who will not be included in the study. These women will undergo clinical pain assessments identical to those proposed for the trial.

The main investigator will perform all IUD placement procedures and postprocedural assessment. This investigator will also undergo specific training for the following outcomes: anxiety, using the Generalized Anxiety Disorder 7 (GAD-7) questionnaire; quality of life, using the WHOQOL-Pain instrument; and patient satisfaction, using a questionnaire based on the method proposed by Lopes *et al.* (2015) [6].

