### Allocation (Sequence generation, allocation concealment mechanism, implementation)

A random sequence generator available online (https://www.sealedenvelope.com/) will be used to select the block randomization option with two treatments at a 1:1 ratio, resulting in equal numbers of patients in each group (n = 36 per group). As the total sample size is 72 patients, 12 blocks of six patients each will be established. Opaque envelopes will be sequentially numbered (1–72) and will contain the randomized group allocation. These envelopes will be sealed and stored securely until the IUD is placed. Only the designated researcher responsible for treatment will be aware of the assigned intervention. After opening, the envelope will be resealed and stored with the patient’s medical record, remaining concealed until the final statistical analysis. An individual not directly involved in the study will generate the random sequence and prepare the envelopes.

All participants will undergo the same IUD placement protocol performed by the same healthcare provider, as described in the “IUD Placement Protocol” section. Immediately after placement, the researcher in charge of applying PBM will retrieve and open an envelope, maintain the order of the remaining envelopes, and administer the assigned treatment (active or sham PBM). Only this researcher will be aware of the allocation.

The main investigator will oversee data storage (digital platforms) and organization. The statistician will be responsible for data analysis and will remain blinded to the interventions. The envelopes will also store participant records (patient history questionnaire, demographic data, risk factors, and statement of informed consent) and will be securely archived.

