**Fig 2 pone.0349031.g002:**
[figure not shown]
Flowchart of study.

Control group – PBM simulation (n = 36 participants): All participants in this group will undergo the conventional IUD placement procedure, as described above. They will receive sham PBM and be treated the same as the experimental group. The researcher in charge of the PBM application will simulate irradiation by positioning the device in the exact location as in the experimental group, but the equipment will be switched off. To prevent the participants from identifying the group to which they belong, the activation sound of the device (beep) will be pre-recorded and played during the sham application.Experimental group – active PBM (n = 36 participants): All participants will undergo the same IUD placement procedure. For irradiation, an LED panel from Sportlux^®^ (Brazil, SP) (Fig 3) will be used. The equipment description, dosimetric parameters, and number of PBM applications are detailed in Table 1.

**Table 1 pone.0349031.t001:** Dosimetric Parameters Used for Preventive PBM.

Technical Parameters	Values
Light source	LED **_**
Application technique	Contact
Wavelength	132 LEDs at 660 nm/ 132 LEDs at 850 nm
Spectral band	20 nm
Beam area on target	0.5 cm²
Irradiation time	20 min
Average power per LED	8 mW
Irradiance	16 mW/cm²
Application time	10 minutes
Energy per LED	4.8 J
Radiant exposure	9.6 J/cm²
Light emission angle	120°

nm- nanometro, W- Watt, J- Joule.

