**Fig 3 pone.0349031.g003:**
[figure not shown]
Sportlux^®^ LED panel used for preventive irradiation during IUD placement. Legend: Source: Created by the authors. Figure A: Panel switched off. Figure B: Panel switched on.

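### The stated basis for blinding participants is not credible as written, and the assessor-absence rule cannot be kept for the early pain scores under either stated PBM timing

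*Protocol article*

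**What the plan says.** All references are to the protocol article.

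- **Participant blinding.** The Blinding (Masking) section states: "The participants will be blinded because of the visual similarity of the treatments (LED on versus LED off".
- **Sham and active panel.** Under Group composition, the sham device is put in the same place as the active one, "but the equipment will be switched off". Its activation beep "will be pre-recorded and played during the sham application". Table 1 lists the active source as "132 LEDs at 660 nm/ 132 LEDs at 850 nm", applied in contact, with a 120° emission angle. The Fig 3 legend describes separate views of the panel off and on.
- **Who assesses.** Calibration/Training states: "The main investigator will perform all IUD placement procedures and postprocedural assessment". The Blinding section says that the researcher who collects outcome data is blinded and "will not be present in the room during treatment".
- **When PBM is given.** The Allocation section keeps envelopes sealed until the IUD is in place, and has the PBM researcher open one and treat straight afterwards. The Fig 3 legend instead describes an "LED panel used for preventive irradiation during IUD placement".
- **How long.** Table 1 gives an irradiation time of 20 minutes and an application time of 10 minutes.
- **VAS schedule.** There are eight scores: baseline, Pozzi clamping, hysterometry, placement, 5 and 15 minutes, and 24 and 48 hours.
- **Records.** Of the envelopes that hold the allocation, the Allocation section adds: "The envelopes will also store participant records".

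**The concern.** The primary outcome is pain that the woman marks herself, so masking her is the main protection against expectation effects. The document rests that masking on a likeness between a lit and an unlit panel. It describes nothing that hides or imitates the light.

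The second protection is a blinded outcome collector who stays away during treatment. The document's own assignment of roles, PBM timing and VAS times do not allow this for the earliest post-placement scores.

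If the woman or the assessor learns the arm, any resulting shift in the scores would be read as an effect of PBM. The analysis could not remove it afterwards.

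**Working it through.** No sample-size or error-rate calculation applies. The check compares sections and sets the PBM duration against the VAS clock.

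**1. Light.** Active arm: 132 LEDs at 660 nm plus 132 at 850 nm = 264, so half emit visible red light. Sham arm: none lit. Matched between arms: position and sound. Not matched, and not described as hidden: the light. The claim of visual similarity therefore has no support in the document. It would be harmless only if the panel were out of the woman's sight, which is not stated.

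**2. PBM straight after placement (Allocation section).** Take placement as minute 0.

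| Duration in Table 1 | PBM runs | 5-min VAS | 15-min VAS |
|---|---|---|---|
| 10 min | 0 to 10 | during PBM | after PBM |
| 20 min | 0 to 20 | during PBM | during PBM |

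A short set-up delay does not help: any start before minute 5 leaves the 5-minute score inside the application. The gap between the two scores is 15 − 5 = 10 minutes. Even a 10-minute application would fit between them only with no slack, and a 20-minute one would not fit. Whoever takes a score during PBM is either in the room, against the Blinding section, or is the PBM researcher, who knows the arm.

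**3. PBM during placement (Fig 3 legend).** The main investigator is inserting the IUD and so is in the room with the panel. The same person is assigned the postprocedural assessment. The absence rule fails again.

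**4. PBM finished before insertion.** This would satisfy the absence rule, but the envelopes stay sealed until the IUD is placed, so the Allocation section excludes it.

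**5. The two durations.** Per-LED energy is power × time, and radiant exposure is irradiance × time.
- 10 min: 8 mW × 600 s = 4.8 J; 16 mW/cm² × 600 s = 9.6 J/cm².
- 20 min: 8 mW × 1200 s = 9.6 J; 16 mW/cm² × 1200 s = 19.2 J/cm².

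Table 1 prints 4.8 J and 9.6 J/cm². These agree with its 10-minute row and not with its 20-minute row. This does not show which row is intended; the authors must reconcile them.

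**6. Which outcomes are exposed.**
- Post-placement timing: baseline, Pozzi, hysterometry and placement (4 of 8 scores) are taken before the envelope is opened, so knowledge of arm cannot affect them. The 5-minute, 15-minute, 24-hour and 48-hour scores (4 of 8) are exposed, together with analgesic use, post-procedure anxiety and satisfaction.
- During-placement timing: the three insertion scores are exposed as well, and baseline too if it were taken with the panel already in use.

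**The case against.** Several points on the other side are sound.

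- **The panel may be out of sight.** Application is in contact, and the exclusion criteria point to the lumbar region. A panel against the lower back of a woman lying down could be hidden from her. A reader might infer that participants will be unblinded; the document does not establish that. What stands is that it relies on visual similarity rather than on concealment, and describes no light shielding.
- **One person inserting and assessing is not unblinding in itself.** It matters only through the timing. The text also speaks of a single examiner for pain calibration and of an unnamed collector of outcome data, so that the main investigator takes every VAS score is partly inference. Under post-placement timing the clash does not depend on this, because the absence rule binds any collector.
- **The during-placement reading rests on one figure legend.** That is true, and Figs 1 and 2 are not shown. The post-placement timing produces a conflict without it.
- **The envelope.** A reader might infer that handling records reveals the arm. The opened envelope is resealed and meant to stay concealed until the final analysis. The listed contents are history, demographics, risk factors and consent, not pain forms. The main investigator's storage role is described for digital platforms. This leaves a minor weakness of storage practice.

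**Conclusion.** The point holds on two counts.

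1. The visual-similarity sentence is not a credible basis for blinding a self-marked pain score.
2. The assessor-absence rule cannot be kept for the 5-minute score, nor for the 15-minute score if PBM lasts 20 minutes, when PBM follows placement. If PBM runs during placement, it cannot be kept by an inserter who also assesses.

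The reach is four of eight VAS scores plus analgesic use, anxiety and satisfaction under the Allocation section's timing, and wider only under the Fig 3 timing. A claim that the whole primary outcome is compromised goes too far.

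A reader might also want an inflated false-positive rate. The document gives neither a VAS standard deviation nor an expected bias, so no such figure can be supported. The conclusion assumes only that 660 nm light is visible and that scores are taken at their stated times. The change should be made before recruitment, since blinding lost during the trial cannot be restored in the analysis.

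**What to change.** 1. Use the same opaque cover over the back and edges of the panel in both arms, so that neither the woman nor the assessor can see light. Replace the visual-similarity sentence with a description of this.
2. Have the authors reconcile the Allocation section with the Fig 3 legend on when PBM is given, and the two durations in Table 1. The next step depends on this.
3. Then state who takes each VAS score and where that person is during PBM, in a form that fits the VAS times. Where presence is unavoidable, say that the opaque cover is what keeps the assessor blinded.
4. Minor: keep the opened allocation slip in a sealed file held by the PBM researcher, apart from participant records.
5. Optional: ask the woman and the assessor to guess the arm, and report the answers.

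Cost: a cover, a separate file, some rewording and slightly longer set-up. No extra staff are needed.

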### Inclusion and exclusion criteria

The study will include women aged 18–50, with no restrictions on race or socioeconomic status. Both nulliparous and multiparous women will be considered eligible, provided they meet other criteria established to ensure the safety and appropriateness of the IUD placement procedure.

Conversely, women with suspected or confirmed pregnancy, a history of diagnosed chronic pain, or active pelvic infection will be excluded from the study. Women who took pain medication within 12 hours before the procedure will be excluded to prevent interference with pain perception. Women with known contraindications for IUD placement, such as significant uterine cavity distortion, active pelvic inflammatory disease, or Wilson’s disease, will be deemed ineligible [4]. Other exclusion criteria include copper allergy, unexplained abnormal uterine bleeding [4], a history of photosensitivity, or any condition affecting the lumbar region, such as active neoplasms, established osteomyelitis, or pre-existing deep tissue injuries with necrosis or infection. The participants will not be permitted to participate in any other clinical study during the trial.

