### Outcome variables

#### Primary outcome.

Pain – Assessed using the Visual Analog Scale (VAS) at baseline, during the IUD placement phases (Pozzi, hysterometry, and IUD placement), 5 and 15 minutes after placement as well as 24 and 48 hours after the procedure.

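### The protocol grounds participant blinding on a lit and an unlit LED panel looking alike, which its own device description contradicts; unblinding is a credible risk for part of the self-reported pain outcome

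*Protocol article*

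**What the plan says.** All places are in the protocol article.

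- **Blinding (Masking)** gives one reason why participants are blinded: "The participants will be blinded because of the visual similarity of the treatments (LED on versus LED off". It also keeps the outcome collector out of the room during treatment.
- **Group composition** puts the sham panel in the same position as the active one, "but the equipment will be switched off". The one cue reproduced in the sham arm is sound: "the activation sound of the device (beep) will be pre-recorded and played during the sham application".
- **Table 1** lists "132 LEDs at 660 nm/ 132 LEDs at 850 nm" at 8 mW per LED, a 120° emission angle and contact application.
- **Fig 3 legend** presents the two states as separate pictures, "Figure A: Panel switched off. Figure B: Panel switched on", and describes an "LED panel used for preventive irradiation during IUD placement".
- **Inclusion and exclusion criteria** rule out "any condition affecting the lumbar region". This is the nearest the text comes to naming the site of application.
- **Primary outcome** is "Pain – Assessed using the Visual Analog Scale (VAS) at baseline", at the three insertion steps, and at 5 min, 15 min, 24 h and 48 h.
- **Allocation** has the envelope opened and the treatment given straight after placement. The Introduction and the Fig 3 legend call the irradiation preventive or place it during insertion.

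**The concern.** A panel with 132 visible-red LEDs switched on does not look like the same panel switched off. The property on which participant blinding is said to rest is one that the device description denies, and the recorded beep deals with sound only.

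This matters because the main outcomes are self-reported. VAS pain, satisfaction and the use of as-needed tablets can all respond to what a woman believes she received. If some women can tell a lit panel from a dark one, part of an active-versus-sham difference may be expectation and not photobiomodulation, and no later analysis could cleanly separate the two.

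**Working it through.** **1. Stated reason against device description.**

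| Cue | Active arm | Sham arm | Source |
|---|---|---|---|
| Visible light | 132 LEDs at 660 nm, 120° angle | none, panel off | Table 1; Group composition |
| Near-infrared light (not visible) | 132 LEDs at 850 nm | none | Table 1; Group composition |
| Sound | device beep | recorded beep | Group composition |
| Position | contact | same position | Table 1; Group composition |

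Sound and position match; visible light does not. Emitted power in the active arm is 264 × 8 mW = 2.11 W, of which 132 × 8 mW = 1.06 W is visible, against zero in the sham arm. These figures confirm that the two states differ. They do not measure how much light a woman would see with the panel against her skin.

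**2. Which scores are exposed.** There are eight VAS scores.

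- *Treatment after placement (Allocation section).* Baseline, Pozzi, hysterometry and placement come before the panel is applied, so seeing it cannot move them. The other four (5 min, 15 min, 24 h, 48 h) can be affected, as can satisfaction at 15 min and tablet use to 48 h. Table 1 gives both 10 and 20 minutes for the session. Under either, a session begun straight after placement is still running at the 5-minute score.
- *Treatment before or during placement (Introduction, Fig 3 legend).* The three insertion scores are exposed as well.

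Part of the primary outcome is exposed under either reading.

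**3. Illustrative size.** The documents give no VAS standard deviation and no expectation effect, so both are assumed here. Inputs: 36 per arm (Allocation section), no true effect, and one two-sided 5% comparison of means. If belief alone shifts the mean difference by d standard deviations, the test statistic follows a noncentral t with 70 degrees of freedom and noncentrality d × √(36/2) = d × √18.

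- d = 0.2: noncentrality 0.85, rejection rate 13.3%
- d = 0.4: noncentrality 1.70, rejection rate 38.8%

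A normal approximation gives 13.6% and 39.6%. In VAS points:

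| Assumed SD | Shift of 0.5 points | Shift of 1.0 point |
|---|---|---|
| 2.0 | 18.2% | 55.3% |
| 2.5 | 13.3% | 38.8% |
| 3.0 | 10.7% | 28.6% |

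The shift is a group average. If only half the women in each arm could tell, and belief made a 1.0-point difference among them, the group shift would be about 0.5 × 1.0 = 0.5 points. The t calculation stands in for the Mann-Whitney and Friedman tests that the Statistical analysis section names.

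**The case against.** The strongest reply is that the woman may never see the light. Application is by contact, the exclusion criterion points to the lumbar region, and she lies down for about 15 minutes after placement. With the emitting face against her back, little light may reach her eyes. This stands, and it limits the conclusion to a risk. It does not rescue the sentence: the article claims that the two states look alike, not that the panel is out of sight, and it does not state the site outright.

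A second reply is that a journal article condenses a fuller protocol, which is cited as a supplement and not shown here. Drapes, eye covers or an allocation guess may be specified there, so their absence is not itself a fault. What remains is a reason that is stated and wrong.

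A reader might also infer more than the documents support:

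- *That participants will be unblinded.* Visibility is not established, and the two pictures in Fig 3 show the panel, not what a woman in position would see.
- *That warmth gives the arm away.* The documents contain nothing about device warmth.
- *That the whole primary outcome is compromised.* If treatment follows placement, four of the eight scores come before it.
- *That the assessor sees the panel.* The Blinding section keeps the collector out of the room. The Calibration/Training section does give placement and post-procedural assessment to the main investigator, which is hard to square with irradiation during placement, or with a 5-minute score taken while the session runs. That is a separate contradiction about timing and roles, to be reconciled in its own right.

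**Conclusion.** The point holds in limited form. The stated basis for participant blinding is contradicted by the sham description and Table 1, and this does not depend on any assumption beyond 660 nm being visible. That women would actually be unblinded is a credible risk, given contact use at what appears to be a lumbar site. It bears on four of the eight VAS scores, satisfaction and analgesic use if treatment follows placement, and on the insertion scores too if it does not.

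The false-positive rates of about 13% and 39% show what an average expectation shift of 0.2 or 0.4 SD would do to one comparison. They rest wholly on those assumed shifts and are not an estimate of the bias in this trial. The point deserves correction before recruitment, because the trial is presented as double-blind and its main outcome is subjective.

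**What to change.** 1. Replace the visual-similarity sentence with a description of masking that can work: hide the light in the same way in both arms, by an opaque drape over the panel and its edges, opaque eye covers for every participant, or both. Active exposure stays unchanged. A barrier used only in the sham arm is best avoided, because it could add a difference in feel. If the full protocol already conceals the panel, state that as the reason for blinding.
2. After the 15-minute ratings, ask each participant and the blinded data collector to guess the allocation, and report the guesses by arm.
3. Reconcile the Introduction, Calibration/Training, Allocation, Blinding (Masking) and Fig 3 legend on when the panel is applied and who collects each score.

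The cost is slightly more set-up time and one extra question for each participant and for the collector. The article reports the trial as not yet recruiting, with an anticipated start of March 30, 2026. If that status still holds, the change can be made by amendment without loss of data.

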### IUD placement protocol according to the recommendations of the ministry of health

Before the procedure, the steps will be explained to the patient again to reduce anxiety and promote relaxation during IUD placement. A two-hand pelvic examination will be performed to assess the size, position, and mobility of the uterus. Infection prevention measures will be implemented, including the use of sterile gloves and cervical cleansing with a chlorhexidine-based antiseptic. The anterior lip of the cervix will be gently grasped with Pozzi forceps to ensure stabilization during placement. A hysterometer will be introduced slowly and carefully to determine uterine depth and angulation, thus minimizing the risk of perforation. During IUD preparation, all instruments and gloves will be maintained sterile, and the device will be assembled according to the manufacturer’s instructions, with the arms kept horizontal during insertion. The retractable technique will be used for placement. The insertion tube will be advanced to the uterine fundus. The tube will then be partially withdrawn while keeping the plunger fixed, thereby releasing the arms of the IUD. After a few seconds, the plunger and insertion tube will be removed. The IUD strings will be trimmed to 2–3 cm from the cervix. The patient will remain lying down for approximately 15 minutes to reduce discomfort. Following placement, the patient will be monitored for well-being and possible vasovagal reactions (e.g., sweating, nausea, or fainting), which are rare and self-limiting. The length of the IUD strings relative to the cervix will be documented in the medical record. The patient will be instructed to return for a follow-up visit in 30 days to verify IUD positioning and adaptation.

